#### Economic data

The acceptability of the draft AD-SUS and the HRQoL measure (EQ-5D-5L) will be explored using completion rates (proportion of randomised participants who completed the AD-SUS or EQ-5D-5L, respectively). The comprehensiveness of the draft AD-SUS will be assessed through the identification of redundant items (services included in the AD-SUS with little or no use reported by participants) and missing items (services not included in the AD-SUS but reported by participants under ‘other’). This data will be used to produce a modified version of the AD-SUS suitable for a subsequent RCT. Service use and HRQoL will be summarised and reported descriptively (mean, SD, ranges, etc.).

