### Assessment procedures

Online screening, consent and baseline assessment will be carried out before randomisation. Following the baseline assessment (week 0), eligible participants will be randomly allocated to either the FREED-M intervention or the control group. Participants in both groups will then complete three brief assessments (weeks 1–3), a post-intervention assessment (4 weeks post-randomisation) and a follow-up assessment (12 weeks post-randomisation); all of these will be completed online.

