### Outcome measures

#### Feasibility outcomes

Primary feasibility outcome: attrition rates at follow-up (the proportion of randomised participants who did not complete the follow-up assessment)Other feasibility outcomes: participant recruitment (proportions of randomised participants recruited from different sources; number of participants recruited per month); completion rates (proportion of randomised participants who completed all assessments); intervention uptake (proportion of randomised participants who accessed at least a part of the first intervention module); intervention completion rates (proportion of randomised participants who accessed each intervention module); intervention acceptability (proportion of participants in the intervention group with a rating of ≥ 4 on each feedback question, scored on a five-point Likert scale from 1 = did not like it at all/ not at all useful to 5 = best thing ever/extremely useful).

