#### Health-related quality of life outcomes

The adult, five-level version of the EuroQol measure (EQ-5D-5L) will be completed at baseline and 12-week follow-up to assess health-related quality of life (HRQoL). This version of the EQ-5D was selected because it was introduced to improve the sensitivity of the measure [86] and, despite being a measure for adults, is recommended by the EuroQol group for participants aged 16 and older [87]. Given the age range in the current study, we will assess the acceptability of this measure for our study participants.

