#### Intervention/service-related outcomes

A modified, self-report version of the Adult Service Use Schedule (AD-SUS) will be tested for acceptability and comprehensiveness at baseline and week 12, in line with previous versions developed for application to both children and young people and young adults [88]. The measure was adapted based on existing evidence of service use in EDs [89, 90]. Service use will be collected from the NHS and social services perspective preferred by the National Institute for Health and Care Excellence (NICE), including education-based health and social services. The feasibility of ascertaining NHS secondary care service use information from electronic patient records at participating ED services will also be assessed.Questions regarding the use of resources from the ED charity website will be asked to both groups at week 4 and 12, and intervention feedback questions will be asked to the intervention group only at week 4.

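### Acceptability of the AD-SUS and EQ-5D-5L is scored over all randomised participants, so the week-12 figure mixes retention with acceptability and the baseline figure leaves out those who stopped before randomisation

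*Protocol article*

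**What the plan says.** In the protocol article, the Economic data section states the purpose and the metric together: "The acceptability of the draft AD-SUS and the HRQoL measure (EQ-5D-5L) will be explored using completion rates". It then defines those rates with all randomised participants as the denominator: "completion rates (proportion of randomised participants who completed the AD-SUS or EQ-5D-5L, respectively".

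The section on health-related quality of life outcomes explains why the question is asked for the EQ-5D-5L, an adult measure used here from age 16: "Given the age range in the current study, we will assess the acceptability of this measure for our study participants".

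Both instruments have the same two time points. The EQ-5D-5L "will be completed at baseline and 12-week follow-up to assess health-related quality of life (HRQoL"; the AD-SUS "will be tested for acceptability and comprehensiveness at baseline and week 12".

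Two other statements matter. The primary feasibility outcome is "attrition rates at follow-up (the proportion of randomised participants who did not complete the follow-up assessment", which uses the same denominator. The Assessment procedures section fixes the order of events: "Online screening, consent and baseline assessment will be carried out before randomisation".

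**The concern.** Acceptability of a questionnaire means whether people who are presented with it will fill it in. A rate over all randomised participants answers another question: how many enrolled participants yield a usable form.

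At week 12, a participant who has left the study counts against the instrument even though they never saw it then. At baseline the problem runs the other way. A person who gives up during the assessment, perhaps at one of these forms, is not randomised and so drops out of the calculation.

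The results are meant to inform the future trial, and the Economic data section says they will help produce a modified AD-SUS for it. For the EQ-5D-5L, this rate is the only quantitative acceptability measure the article states. Read on its own, it could make a well-accepted form look poor at week 12 and hide early drop-out at baseline.

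**Working it through.** **Inputs from the article.** Total N = 116, that is 58 per group, and assumed attrition a = 0.40 (Sample size). Attrition above 50% is a stop criterion (Progression to full trial). The article gives no completion rate among those who reach an assessment. That quantity, c, is an assumption, shown from 0.70 to 1.00. The definition names no time point, so it is applied to each in turn.

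**The plan's own figures.** 35/(1 − 0.40) = 58.3 per group, and 70/0.60 = 116.7 in total, against the stated 58 and 116. The half-width for 40% attrition is 1.96 × √(0.40 × 0.60/116) = 0.089, against the stated ±9%. Both reproduce within rounding.

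**Week 12.** Rate over randomised = (1 − a) × c.

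| Attrition a | c = 1.00 | c = 0.95 | c = 0.90 | c = 0.80 | c = 0.70 |
|---|---|---|---|---|---|
| 0.20 | 80% | 76% | 72% | 64% | 56% |
| 0.30 | 70% | 66.5% | 63% | 56% | 49% |
| 0.40 | 60% | 57% | 54% | 48% | 42% |
| 0.50 | 50% | 47.5% | 45% | 40% | 35% |

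- In the first column the instrument is fully accepted throughout, yet the rate falls from 80% to 50% through attrition alone.
- At a = 0.40, a shortfall of 10 points among those reached appears as 60 − 54 = 6 points, beneath a 40-point loss from attrition.
- Without the attrition figure, an observed 57% fits c = 0.57/0.60 = 0.95, c = 0.57/0.70 = 0.81 or c = 0.57/0.80 = 0.71.

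**With the denominator changed.** About 116 × 0.60 ≈ 70 participants reach week 12, and the rate becomes c itself. The 95% half-width, 1.96 × √(c(1 − c)/70), is 5 points at c = 0.95, 7 points at c = 0.90 and 9 points at c = 0.80.

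**Baseline.** The denominator holds only people who got past the baseline assessment and were randomised. Those who stopped at or before these forms are in neither numerator nor denominator, so the rate is biased upwards as a measure of acceptability. The size cannot be computed: the article gives no number of starters and does not say whether an instrument may be skipped.

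**The case against.** The strongest reply is that little is lost. Attrition is the primary feasibility outcome, has the same denominator and will be reported, so a reader can divide: 54/60 = 90%. The two instruments share denominator and time points, so attrition cancels when one is compared with the other. The measure is only to be explored. It has no threshold and is not a progression criterion, and the AD-SUS is also examined for redundant and missing items. Completion per randomised participant also has a proper use, since it tells a future trial how much economic data to expect per person enrolled.

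Most of this stands and limits the severity. A reader might infer that acceptability cannot be separated from attrition at all, or that the choice of instruments for the full trial depends on this one rate. The article supports neither.

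The division is not quite clean, however. The Progression to full trial section defines attrition as having no follow-up assessment, while the Feasibility outcomes section counts those who did not complete it. Under the second wording, someone who starts week 12 and stops at the AD-SUS may count as attrition, and the derived completion rate would then be too high. Nor does division help at baseline.

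A reader might also infer that baseline completion must be close to 100%. The article gives only the order of baseline and randomisation. If forms can be skipped, the baseline rate could be lower and would carry some information.

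Finally, the age range is the stated reason for the EQ-5D-5L question, but the article promises acceptability for the participants as a whole. An age split would be a preference, and its absence is not an error.

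**Conclusion.** The point holds in a limited form. The article fixes a denominator that does not match the stated purpose, so this is more than detail left to another document. At week 12 the rate is retention times instrument completion. At the planned 40% attrition it is capped at about 60%, and it is 54% if 10% of those reached do not complete the form. At baseline the rate is biased upwards by an unknown amount.

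The week-12 figures rest on the article's 40% attrition, on assumed values of c, and on counting as retained everyone who completes the instrument at week 12. If people who complete an instrument but not the whole assessment are counted as lost, the cap would be somewhat looser. Severity is modest, because the measure is descriptive and secondary and the week-12 conditional rate is largely recoverable from reported attrition.

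**What to change.** In the Economic data section, define acceptability as the proportion completing each instrument among participants who started that assessment, reported separately for baseline and week 12. If starts are not logged, use participants who returned any part of the assessment. At baseline, include starters who were not randomised, where the platform records them. Keep the rate over all randomised beside it, labelled as data availability.

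In the example above, the reported week-12 acceptability would change from 54% to 90%, with the 54% still shown for planning.

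The cost is a little extra reporting and a check that the platform logs assessment starts, which the article does not state. N = 116, the progression criteria and the design are unchanged.

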#### Qualitative data

We will use framework analysis to facilitate analysis both within and across young people [94–96]. The interpretivist assumptions underpinning our approach emphasise the importance of understanding individuals’ experiences and interpretations from their points of view. No specific theory will be used to guide the development of the coding framework. However, given the semi-structured nature of the topic guide, this is likely to influence the generation of the initial framework used to code the interviews. In short, transcripts will be reread to ensure data familiarisation. Two researchers will independently code a minimum of five transcripts and discuss alternative viewpoints before reaching a consensus on a provisional analytical framework to be applied to subsequent transcripts. An iterative method, in which the data extracts are continuously checked for coherence and the coding framework refined, will be followed. Data will be summarised through charts to map the range of views and experiences and to allow the wider research team to engage with and offer interpretations of the data.

### Patient and public involvement

In preparation for the first stage of the protocol development, we conducted a focus group with five young adult ED patients to identify topics for psychoeducation and how this should be delivered. Three experts by experience reviewed different proposal stages. The animations and resources included in the intervention were developed iteratively in consultation with ED clinicians and young people in our target age range, current patients and/or those with current or prior lived experience. Two patients/experts by experience will be part of the trial steering group. Jointly with the core research team, they will: be involved in aspects of study design, oversee the running of the study, be involved in designing a future large-scale RCT by appraising findings from the feasibility study, and contribute to dissemination. In addition, other young people will be involved in beta-testing and dissemination on an ad hoc basis. These will be recruited from our volunteer registry of FREED patients (FREEDom Finders) and via social media. Participation will be balanced in terms of gender, age and ethnicity. Patient consultants to the project will be remunerated in line with INVOLVE guidance [97].

## Ethics and dissemination

### Ethics and safety consideration

This trial will be conducted in compliance with the Declaration of Helsinki, the principles of good clinical practice (ICH-E6 guideline), and the ICH-E8 and E9 guidelines, and in accordance with all applicable regulatory requirements including but not limited to the UK policy framework for health and social care research. The results of this trial will be reported in accordance with the CONSORT 2010 Statement [98]. This trial is registered in the ISRCTN register (ISRCTN15662055). Ethical approval was obtained from the London-Camden & Kings Cross Research Ethics Committee (REC Ref: 22/LO/0655) on 11th October 2022.

We are aware that some young people joining the trial may experience significant distress and/or suicidal symptoms. Irrespective of which group they are allocated to, each page of the intervention will display a clickable button that reads ‘I need urgent help’. Clicking this button will signpost them to the Young Minds urgent help page (https://www.youngminds.org.uk/young-person/find-help/i-need-urgent-help/), which provides details of confidential support and crisis hotlines for young people in distress or at risk of suicide.

### Dissemination plan

This novel intervention has the potential to substantially improve help-seeking and ultimately reduce DUED. If successful, and after carrying out a future large-scale trial, we would disseminate the intervention widely in NHS (including both primary and secondary care), community and education settings.

We will disseminate our findings to young people and families via relevant organisations. This will include conference presentations and information on the websites of these organisations and other relevant websites (such as FREEDfromED.co.uk, EDIFYresearch.co.uk, and the King’s College London websites). To reach young people, we will post information on social media feeds (e.g. Instagram, Facebook and Twitter®) of relevant organisations and selected influencers. Finally, we will work with our press office to disseminate the work to the press and other media outlets.

We will disseminate our findings to schools and universities via relevant organisations/conferences (e.g. Personal, Social, Health and Economic Education (PSHE) teachers’ organisation, schools in Mind Network) and student mental health and well-being organisations.

We will disseminate study findings to health professionals via scientific papers and relevant conferences such as large UK and international primary care, early intervention and ED conferences. We will work with Academic Health Sciences Networks (AHSNs) to facilitate the adoption and spread of our FREED-M innovation across all areas of healthcare provision. We will work towards getting our intervention adopted into NHS Mental Health online resource libraries and endorsed/recommended by relevant national and international guidance documents/organisations.

### Trial progress

Participant recruitment and data collection for this study began in November 2022. Amendments to the study protocol will be reported in publications reporting the study outcomes.

## Data Availability

Not applicable.

## Abbreviations

AD-SUS: Adult service use schedule
AHSN: Academic Health Sciences Networks
BMI: Body mass index
DES: Disclosure expectations scale
DUED: Duration of an untreated eating disorder
ED: Eating disorder
EDDS: Eating Disorder Diagnostic Scale
GP: General practitioner
HRQoL: Health-related quality of life
FREED: First Episode Rapid Early Intervention for Eating Disorders
FREED-M: First Episode Rapid Early Intervention for Eating Disorders-Mobile
LGBTQ +: Lesbian, gay, bisexual, transgender, queer/questioning and others
NHS: National Health Service
NICE: National Institute for Health and Care Excellence
PHQ: Patient health questionnaire
PSHE: Personal, Social, Health and Economic Education
RCT: Randomised controlled trial
UK: United Kingdom
UNICEF: United Nations Children’s Fund
WSAS: Work and Social Adjustment Scale
